**Methods:**

A total of 45 people with PD, between 35 and 85 years old and Hoehn and Yahr stages between I to III, will be recruited from movement disorder centers for this three-armed study. Participants will be randomized into three groups (occupation-based interventions with responsibility feedback, occupation-based interventions without responsibility feedback, and conventional interventions). All participants will receive intervention for 24 sessions during a period of 12 weeks (2 sessions per week). The primary outcome measure will be participation satisfaction. Participation frequency and restriction, self-perceived performance, performance satisfaction, motivation, volition, sense of agency, responsibility, physical activity, community integration, activities of daily living (ADL), instrumental ADL, upper extremity function, balance, fatigue, and quality of life will be measured as secondary outcome measures. All outcomes will be measured at baseline, session 9, session 17, post-intervention (week 13), and follow-up (week 25).

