### Data collection

The assessor (an occupational therapist with 6 years of experience in neurological rehabilitation) will conduct initial screening and outcome measure evaluations at baseline, session 9, session 17, post-intervention (week 13), and follow-up (week 25) (Table 1). Since this is a low-risk study, independent data monitoring and auditing will not be taken into consideration. Written feedback about the results of the evaluations will be provided to all participants in order to promote retention. A recent systematic review suggested that people with PD will benefit from moderate to high doses of intervention (≥ 8 sessions and ≥ 10 weeks) [5]. We will intend to discover the proper dose of intervention by multiple assessments during the treatment process. Treatment sessions will be started 1 or 2 days after the initial screening in participant’s homes for 12 weeks (two times a week) by three experienced occupational therapists (average 5 years of experience). The occupational therapists will be trained for 2 days regarding the study procedures and intervention protocols. Therapists will be allowed to contact the main researcher to share any issues that arisen in the intervention process. Home-based therapy with a focus on meaningful occupations appears to be the most plausible beneficial intervention [27]. Moreover, the environment is more familiar for the patient, and near-ones find it more convenient [41].

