### Randomization and blinding

After obtaining consent and baseline data, an independent researcher who will not be involved in assessments will allocate the participants to each group. Participants will be randomly assigned to each group using a sequence generated by http://www.randomizer.org. For determining concealment, unique codes will be written on envelopes which contain group specifications. The assessor will be blind to the allocation of participants in groups and will enter data in the OT clinic. We do not anticipate any requirement for unblinding but if required, the trial steering committee (i.e., chief investigators and clinical project manager) will have access to the group allocations and any unblinding will be reported. Assessments will be conducted before allocation. Moreover, patients will not know which intervention they are receiving.

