The functional level of each patient will be determined using the Gentile taxonomy. The intervention will be delivered to patients at any level of the taxonomy where they experience challenges. Participants will receive occupations from simple (i.e., stationary condition with no intertrial variability and object manipulation) to hard (i.e., in-motion conditions with intertrial variability and object manipulation) levels based on their priorities identified via Canadian Occupational Performance Measure. All patients will be actively participating in at least three to four occupations. Therefore, all participants will receive the same amount of intervention. The therapists will keep a record of the extent of participation in each occupation using a visual analog scale during each session.

Moreover, feedback statements that have the potential to create a sense of responsibility (i.e., derived from international and national Delphi studies with renowned experts and patients) in patients will be provided to participants as knowledge of performance or knowledge of the result. These feedback statements will be positive or negative statements in relation to the individual or his/her family for prevention/symptom management and function improvement. These feedback statements (i.e., based on type, target, and purpose) will be presented to the patients throughout the intervention sessions. An expert panel was held to sort the feedback statements so that patients receive all forms of feedback in each session. Some examples of responsibility feedback are provided in Table 2.

This group will receive conventional interventions (see below) for 15 min in each session. They will receive occupation-based interventions with responsibility feedback for the remaining 45 to 75 min.

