### Measurements

Demographic and PD-related information including age, gender, education, family status, marital status, job status, assistive device use, fall history, years since diagnosis, and medications will be collected from participants. Outcome measures will be assessed by a blind certified occupational therapist at baseline, session 9, session 17, post-intervention, and follow-up.

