### Secondary outcome measures

Secondary outcomes will include participation frequency and restriction, motivation, and volition as well as sense of agency, responsibility, physical activity, community integration, ADL and IADL, upper extremity function, balance, fatigue, and quality of life.

Several psychometric scales will be employed for these secondary outcome measures, as follows:

Participation frequency and restriction

*Frequency and restriction scales of USER-P* will be regarded for measuring this outcome. The frequency scale consists of two parts. Part A measures the time (0 = not at all; 5 = 36 h or more) spent on paid work, unpaid work, volunteer work, and housekeeping. Part B measures the frequency (0 = not at all; 5 = 19 times or more) of social and leisure activities. The restriction scale evaluates restrictions experienced while participating in daily activities. Items will be scored as not applicable (NA), not possible (1), with assistance (2), with difficulty (3), and without difficulty (4). The sum scores in these two scales will be converted into a 0–100 scale (54).

Self-perceived performance and performance satisfaction

*Canadian Occupational Performance Measure* will be used to evaluate the self-perceived occupational performance and satisfaction with a semi-structured interview in areas of self-care, productivity, and leisure [56].

Motivation

*Social Motivation Questionnaire* will be used to measure the information-seeking (4 items) and emotion-regulatory behavior (4 items) motivation for social participation. Each item will be graded between 1 (very disagree) and 7 (very agree). Higher scores will denote stronger information-seeking and emotion-regulatory behavior motivation [57].

Volition

*Volitional Questionnaire* is a MOHO tool which will evaluate volitional development via observing individuals while performing occupations with 14 items. Items will be rated as follows: 1 = passive, 2 = hesitant, 3 = involved, and 4 = spontaneous. Higher scores will represent a higher level of volition [58].

Sense of agency

*Intentional Binding Task* measures the implicit sense of agency. Subjects will be asked to judge the time of actions (i.e., key press) and effects (i.e., tones) via a clock hand rotating around a clock face on a computer screen. This task contains two baseline (tone, action) and two operant (tone, action) conditions [59].

Responsibility

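### Assessor blinding of the observer-rated secondary outcomes is at high risk for A/B versus C, because the same assessor repeats the occupation interview at four visits after allocation

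*Protocol article*

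**What the plan says.** Under Randomization and blinding, the article says that "The assessor will be blind to the allocation of participants in groups and will enter data in the OT clinic". Measurements extends the claim to every visit: "Outcome measures will be assessed by a blind certified occupational therapist at baseline, session 9, session 17, post-intervention, and follow-up". Data collection describes one assessor, an occupational therapist, who does the screening and all outcome evaluations. The abstract has all outcomes measured at all five time points.

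Three outcome and treatment descriptions matter here:

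- The COPM "will be used to evaluate the self-perceived occupational performance and satisfaction with a semi-structured interview in areas of self-care, productivity, and leisure".
- The Volitional Questionnaire "will evaluate volitional development via observing individuals while performing occupations with 14 items", each item rated from 1 (passive) to 4 (spontaneous). The Dynamic Gait Index has 8 conditions on a 4-point scale. No separate rater is named for either.
- In group A, occupations are graded and delivered "based on their priorities identified via Canadian Occupational Performance Measure". Group B receives the same occupation-based programme without the feedback. Group C receives conventional treatment only.

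The supports given for blinding are an allocating researcher who does no assessments, envelopes with unique codes, patients who are not told which intervention they receive, and this sentence: "Assessments will be conducted before allocation". In addition, treatment is given at home by three other therapists, and patients visit the clinic only for evaluations.

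**The concern.** The COPM has two roles. It is a repeated outcome, and it selects the content of treatment in two of the three arms. After allocation, the person who must stay blind talks with each patient four times about self-care, productivity and leisure. Two thirds of those patients have been practising such occupations at home with a therapist, and one third have been doing exercises. A patient who explains why an occupation has improved may well describe the sessions.

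If that happens, the assessor's ratings of volition and balance can drift in favour of A and B. Volition is part of the trial's rationale (Background), and the Discussion lists self-report as a limitation, so readers may give the observer-rated outcomes extra weight. The report would call the assessor blinded with no information on whether the blinding held.

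**Working it through.** **1. Which visits the timing sentence can cover.** The assessments are baseline, session 9, session 17, week 13 and week 25. Allocation follows consent and baseline data, so 1 of 5 assessments precedes it and 4 of 5 follow it. The sentence placing assessments before allocation can be true of baseline only. With 45 patients there are up to 45 × 4 = 180 assessments after allocation. This counts exposure; it does not measure bias.

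**2. What each other safeguard blocks.**

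- Independent allocation and coded envelopes protect the sequence, not later conversations.
- Home treatment by other therapists separates the assessor from the therapists, not from the patient.
- Not telling patients the name of their arm does not stop them from describing what they do in sessions.

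**3. What the interview could reveal.** Assume it discloses occupation practice versus exercises only, and nothing about feedback. Group C is then identified, and A versus B stays a coin toss. The chance of a correct guess rises from 1/3 to at most (1/3 × 1) + (2/3 × 1/2) = 2/3.

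**4. Which outcomes are exposed.** The Volitional Questionnaire (14 judged items) and the Dynamic Gait Index (8 judged items) are exposed most. The timed 9-Hole Peg Test is exposed less. The primary outcome, USER-P satisfaction, is the patient's own report.

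**5. Illustrative size.** The documents give no bias figure, so 0.2 to 0.3 SD is an assumption. It is applied equally to A and B, with no true effect. Data analysis plans Tukey comparisons after repeated-measures ANOVA. At one time point with n = 15 per arm:

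- Degrees of freedom: 45 − 3 = 42.
- Critical value: the 95% studentized range point for 3 groups is 3.436, so |t| must exceed 3.436/√2 = 2.43.
- Noncentrality for A versus C: bias × √(15/2).

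| Assumed bias | Noncentrality | Probability that the A–C pair is significant |
|---|---|---|
| 0 | 0 | 1.9% |
| 0.2 SD | 0.55 | about 3.7% |
| 0.3 SD | 0.82 | about 6.2% |

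An unadjusted two-sample t-test with 28 degrees of freedom would give 8.3% and 12.5% for the same biases, but that is not the planned comparison.

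**The case against.** The best defence is that the COPM is given to all arms and asks about performance and satisfaction, not about treatment. A and B also receive 15 minutes of conventional treatment per session, so patients in every arm can truthfully mention exercises. The article promises that any unblinding will be reported. Scripts and test order are also details that a condensed article may leave to a fuller document.

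Much of this stands, and it limits the point. A reader might infer more than the documents support in five ways:

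- **That blinding will certainly fail.** Disclosure is likely, not certain.
- **That the whole trial is unblinded.** Nothing in the COPM reveals responsibility feedback, so this route does not break A versus B, and it does not reach the self-reported primary outcome.
- **That the interview precedes the ratings within a visit.** The readable text gives no order, and Table 1 is not shown. From session 17 on, however, an earlier interview after allocation comes before later ratings whatever the order.
- **That the assessor hands COPM priorities to therapists for A and B only, which would be a second leak.** The article does not describe the hand-over, and the COPM is a baseline measure, so priorities can exist for all patients before allocation.
- **That the judged outcomes are the only check on self-report.** The 9-Hole Peg Test and the computer-based Intentional Binding Task are neither questionnaires nor judged ratings.

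The objection about article length does not remove the point. The article makes a blinding claim for all five visits and supports it with a sentence that can hold for one of them. The procedure it describes works against the claim at the other four.

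**Conclusion.** The point holds as a risk, not as a demonstrated failure. Assessor blinding of the Volitional Questionnaire and the Dynamic Gait Index is at high risk for A and B against C at the four visits after allocation. The basis is textual: a single assessor, a repeated interview with the instrument that sets treatment content in A and B, and a timing safeguard that is true at baseline only.

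Any size is conditional. With an assumed bias of 0.2 to 0.3 SD, the false-positive rate per A–C pair rises from about 2% to about 4 to 6%. This assumes Tukey at one time point with 15 per arm; the full repeated-measures test was not modelled. No figure in the sample size section changes. The outcomes concerned are secondary, so this is an inexpensive improvement and not a flaw in the trial's main comparison.

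**What to change.** - **Wording.** Limit the sentence on assessments before allocation to the baseline assessment.
- **Instruction.** At each later visit, read a short fixed text asking patients not to describe their home sessions.
- **Order.** At each later visit, complete the Volitional Questionnaire, Dynamic Gait Index and 9-Hole Peg Test before the COPM. Observe volition on the same set of occupations in all arms.
- **Optional.** Have the assessor record a guess of the arm, and report it. If blinding proves to have failed, describe the A/B-versus-C results on the rated outcomes with caution.

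No extra staff or visit is needed. The costs are a fixed test order, a short script and, if wanted, one form item. Protection is only partial from the second visit after allocation on, because the assessor may remember earlier interviews. The guess data may also mean that the blinding claim has to be softened.

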The concept of sense of responsibility was not considered in the aforementioned studies while delivering interventions. Sense of responsibility refers to the intentional binding mechanism that connects our intentions to the corresponding outcomes. We attribute our own activities to ourselves in this process; hence, we feel a sense of control and accountability [28, 29]. Sense of responsibility is intertwined with agency (i.e., controlling doing of occupations and their consequences) and its neural correlates. These neural correlates (e.g., angular gyrus, insula, supplementary motor area) play a critical role in agency and responsibility [30, 31]. Sense of responsibility and agency are crucial while executing goal-directed occupations [32–34] and may change health-related behaviors, such as non-motor symptoms [35, 36]. Moreover, feedback (knowledge of result or knowledge of performance) may cause behavioral and neurological changes and hence promote participation [37]. This study aims to conduct a trial to compare the efficacy of occupation-based interventions on participation in people living with idiopathic PD in three groups: (1) occupation-based interventions with responsibility feedback, (2) occupation-based interventions without responsibility feedback, and (3) conventional interventions.

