## Methods

### Trial design

A parallel, three-armed, double-blinded (assessor and patients) randomized controlled trial will be conducted. Individuals will be assigned to each group in a ratio of 1:1:1 (group A: occupation-based interventions with responsibility feedback; group B: occupation-based interventions without responsibility feedback; group C: conventional interventions). The CONSORT diagram [38] will present the trial design (i.e., enrollment, allocation, and assessments) in brief (Fig. 1). This clinical trial follows the recommendations for Interventional Trials (SPIRIT) [39] statements (Additional file 1).

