### Participants and recruitment procedures

Community-dwelling individuals with Parkinson’s will be recruited from movement disorder centers and rehabilitation clinics in Tehran, Iran. Advertisements in Iran’s Parkinson Association will be done. Individuals who meet the inclusion criteria (see section below) will receive consent form and information regarding study aims and procedures.

Due to COVID-19 pandemic precautions, patients will only come to the OT clinic for evaluations. All sessions will be free for participants, and travel costs for evaluation will be paid by the research team. Both assessments and interventions will be conducted in the “ON” (1 h after levodopa intake) medication state. Levodopa equivalent dose (LED) will be calculated for individuals in each assessment session using Tomlinson et al. formula [40].

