### Conventional interventions (group C)

All the participants who are assigned to this group will only receive traditional treatment (60 to 90 min), including passive mobilization, lower extremity strengthening, stretching, motor coordination (upper and lower extremity), balance and walking training, manipulation exercises, breathing, relaxation, and postural exercises [52, 53]. Depending on the condition of each patient, they will receive these interventions. The duration and number of each therapeutic intervention will be recorded in each session.

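### Patients are stated to be blinded, but they can see which treatment they receive, and the primary outcome is their own rating

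*Protocol article*

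**What the plan says.** Under Trial design, the protocol article describes a "double-blinded (assessor and patients) randomized controlled trial". Randomization and blinding says the assessor will be unaware of allocation, and adds: "Moreover, patients will not know which intervention they are receiving".

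Other sections bear on this:

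- **Recruitment.** Eligible people "will receive consent form and information regarding study aims and procedures".
- **Aim (Background).** "This study aims to conduct a trial to compare the efficacy of occupation-based interventions on participation in people living with idiopathic PD in three groups". The three groups are then named.
- **Group A.** After 15 minutes of conventional work: "They will receive occupation-based interventions with responsibility feedback for the remaining 45 to 75 min". The occupations follow the patient's own priorities, and all forms of feedback are given in each session.
- **Group B.** The same split of session time and the same occupations, without the feedback.
- **Group C.** Patients "will only receive traditional treatment (60 to 90 min), including passive mobilization, lower extremity strengthening, stretching", with balance, walking, breathing and similar work.
- **Primary outcome.** Participation satisfaction on the USER-P: ten 5-point Likert items, rescaled to 0–100. The inclusion criteria require literacy in Persian so that patients can fill in self-report questionnaires.
- **Limitations (Discussion).** Self-report may lead patients to under- or over-report. This is not linked to knowing one's treatment.

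**The concern.** Blinding of patients is stated as a fact of the design, yet the article describes no sham, no dummy feedback and no withholding of the hypothesis that would produce it. Over 24 sessions, a patient will notice whether the time goes on stretching and balance work or on preparing meals and dressing.

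This matters because of the primary outcome. For a satisfaction rating, the patient is in effect the outcome assessor. A therapist who does not know the allocation can administer the scale neutrally but cannot remove the patient's expectations from the answers. The same holds for other self-rated scales, such as the Canadian Occupational Performance Measure, the Social Motivation Questionnaire, the Fatigue Severity Scale and the PDQ-39.

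If the trial is reported as blinded for patients, readers will take an A–C or B–C difference in satisfaction to be protected from expectation when it is not.

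**Working it through.** **Step 1. Does the text support patient blinding?** The contrasts are taken in turn, from the sections on groups A, B and C.

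| Contrast | Shared | What the patient can see |
|---|---|---|
| A vs C | Session length 60–90 min, two sessions a week, 12 weeks | A: 15 min conventional, then 45–75 min of occupations with spoken statements. C: conventional work throughout |
| B vs C | As above | B: 15 min conventional, then 45–75 min of occupations. C: conventional work throughout |
| A vs B | Same schedule, same conventional part, same occupations | Only the feedback statements |

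For A or B against C, the content of at least 45 minutes of every session differs openly. For A against B, a patient in B would see nothing missing unless told that feedback was under test. The article does not say how that would be kept from them.

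**Step 2. The plan's own figure.** The sample-size section gives f = 0.25, correlation 0.25, power 80%, alpha 5% and a total of 39. With k = 3 groups, m = 5 visits and sphericity (assumed), the group-by-time interaction has λ = f²·N·m/(1 − ρ).

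- λ = 0.0625 × 39 × 5 / 0.75 = 16.25, df 8 and 144, power 0.81. N = 39 reproduces.
- For dropout, 39 × 1.15 = 44.85 gives the stated 45; 39/0.85 = 45.9 would give 46. This does not affect the present point.

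**Step 3. Illustration of an expectation shift.** *Assumption, not in the documents:* no true effect, but self-ratings in A and B lie b = 0.3 to 0.4 SD above C at all four post-baseline visits. Taken from the plan: 15 per arm (45 at 1:1:1), correlation 0.25, two-sided 5%. Sphericity is assumed.

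*Group-by-time interaction.* λ = n·SS/(1 − ρ), where SS is the sum of squared interaction effects over the 3 × 5 cell means. For this pattern SS = (2/3)·b²·(4/5) = 0.533·b².

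- b = 0.3: SS = 0.048, λ = 15 × 0.048 / 0.75 = 0.96. Rejection 8.3%.
- b = 0.4: SS = 0.0853, λ = 1.71. Rejection 11.4%.

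The reference is F with 8 and 168 df.

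*Group main effect.* λ = n·m·SS/(1 + (m − 1)ρ), where SS is taken over the three group means. The mean shift over five visits is 0.8·b, so SS = (2/3)(0.8b)² = 0.427·b².

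- b = 0.3: SS = 0.0384, λ = 75 × 0.0384 / 2 = 1.44. Rejection 16.4%.
- b = 0.4: SS = 0.0683, λ = 2.56. Rejection 26.2%.

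The reference is F with 2 and 42 df.

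*Tukey-adjusted A–C comparison at week 13, baseline-adjusted.* SE = √(1 − 0.25²) × √(2/15) = 0.968 × 0.365 = 0.354 SD. The noncentrality is 0.3/0.354 = 0.85 or 0.4/0.354 = 1.13. Against the Tukey critical value for three groups (about 2.43 on the t scale), rejection is about 7% or 11%. Without any shift, this single comparison rejects about 2% of the time.

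**Step 4. Scale.** If A and B are alike and differ from C by x, then f = x·√2/3. The planning effect f = 0.25 therefore corresponds to x = 0.25 × 3/√2 = 0.53 SD. The assumed shift is smaller than the effect the trial is sized to detect, but of the same order.

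**The case against.** Several points can fairly be made for the protocol.

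- **Assessor blinding is a separate claim.** A reader might infer that the trial has no protection from bias at all. The documents do not support that. Nothing contradicts the statements that the assessor is unaware of allocation, and this can still help performance tests such as the 9-Hole Peg Test and the Dynamic Gait Index.
- **Patients may be unaware of the hypothesis.** All arms receive active therapy of equal length and frequency, and A and B differ only in feedback. Masking to the hypothesis is conceivable, above all for A against B. This stands as a limit on the point. However, the article claims something else, namely that patients do not know their intervention, and it describes no means for either.
- **The consent content is not shown.** A reader might infer that patients are told which arm is expected to do better. The article says only that aims and procedures are explained. It cannot be seen how far the comparison is disclosed, so no fault in the consent wording can be alleged.
- **Self-report bias is already listed as a limitation.** This is true, but it is not tied to knowledge of the arm, and the blinding claim suggests that this tie has been cut.
- **The size is assumed.** This stands. It also depends on the test. An unadjusted, baseline-adjusted A–C test at week 13 would give about 13% to 20% for the same shift, but that is not the planned analysis. The article plans a 3 × 5 repeated-measures analysis with Tukey comparisons, and uses baseline-adjusted regression only if groups differ at baseline.

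**Conclusion.** The statement that patients are blinded is wrong as written. The article's own account of the arms contradicts it, clearly for A or B against C and less so for A against B. Because the primary outcome is the patient's own rating, the blinded assessor does not protect it from expectation.

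The conclusion rests on the text and on no number. The figures only show what could be at stake: under the assumed 0.3 to 0.4 SD shift, about 8% to 11% for the interaction, 16% to 26% for the group main effect and 7% to 11% for a Tukey-adjusted A–C comparison. They do not show that such a shift will occur. Patient blinding is hardly achievable with these treatments, so the fault lies in the claim and not in the choice of interventions.

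**What to change.** - In Trial design, describe the trial as assessor-blinded only.
- In Randomization and blinding, delete the sentence on patients, or replace it with what they are in fact kept unaware of (for example the hypothesis) and how.
- State that the self-rated primary outcome and the other self-rated outcomes are not blinded to treatment.
- In the Discussion, extend the self-report limitation to expectation bias in A–C and B–C differences.

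Optional: ask patients and the assessor at week 13 to guess the arm, and show the assessor-measured tests beside the primary outcome. Those tests measure dexterity and balance, not participation, so they cannot stand in for it.

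The cost is wording, plus one item if the guess is added. The stated level of blinding becomes less favourable. Randomization, sample size and analysis are unchanged.
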